#### Sample size

For the present sample size analysis, a conservative estimate of 0.40 as the between-group effect size on the outcome physical functioning is used. This estimate is based on reported effect sizes on patient-reported outcomes of physical functioning in other studies using technology and coaching on physical activity [26, 27]. Based on alpha = 0.05, power (1 − *β*) = 0.80, a two-sided test for repeated measures with an expected within-subject correlation coefficient of 0.6 and 5 follow-up measurements the minimum number of 67 subjects per group is required, with a total sample size of 134 (see Formula 1). Allowing for a drop-out rate of 20% during the study, this study should include 161 patients.

The most important secondary outcome of this study is objectively measured physical activity. Therefore, a sample size calculation was also made on this outcome measure. Based on the effect sizes found in our recent systematic review and meta-analysis of interventions using activity trackers in patients during or after inpatient stay on the outcome physical activity, an effect size on physical activity of 0.50 is expected [22]. Based on alpha = 0.05, power (1 − beta) = 0.80 and a two-sided test the minimum number of subjects required is *n* = 128 (64 in each group). Allowing a drop-out rate of 20% during the study, a total of 154 patients should be included.

Formula 1:

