**Methods:**

In this multicenter single-blinded randomized controlled trial, 161 adult patients scheduled for elective gastrointestinal or lung cancer surgery will be randomly assigned to the intervention or control group. The purpose of the Optimal Physical Recovery After Hospitalization (OPRAH) intervention is to encourage self-management of patients in their functional recovery, by using a smartphone application and corresponding accelerometer in combination with coaching by a physiotherapist and dietician during three months after hospital discharge. Study outcomes will be measured prior to surgery (baseline) and one, four, eight, and twelve weeks and six months after hospital discharge. The primary outcome is recovery in physical functioning six months after surgery, and the most important secondary outcome is physical activity. Other outcomes include lean body mass, muscle mass, protein intake, symptoms, physical performance, self-reported limitations in activities and participation, self-efficacy, hospital readmissions and adverse events.

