#### Randomization and blinding

After the baseline measurements, patients will be randomly assigned to the control or intervention group with a 1:1 allocation ratio using the randomization tool of Castor Electronic Data Capture (EDC) [25]. Randomization will be stratified per center by type of surgery (lung, HPB, upper GI, colorectal) and ASA score (1–2 or ≥ 3). The randomization tool of Castor ensures concealment of allocation. The researcher informs the participant by e-mail which group he has been assigned to. Assessments will be conducted by a blinded research assistant. Neither the patient nor the therapist will be blinded.

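### The drop-out allowance multiplies by 1.20 instead of dividing by 0.80: 161 patients less 20% leaves about 129, not the 134 the plan requires

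*Protocol article*

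**What the plan says.** The Sample size section of the protocol article sizes the trial on physical functioning. It states that "a conservative estimate of 0.40 as the between-group effect size on the outcome physical functioning is used", with two-sided alpha 0.05, power 0.80 and "an expected within-subject correlation coefficient of 0.6 and 5 follow-up measurements". From these it obtains 67 per group, 134 in total, which it calls the minimum. It continues: "Allowing for a drop-out rate of 20% during the study, this study should include 161 patients".

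A second calculation covers physical activity, named as the most important secondary outcome. An effect size of 0.50 gives 128 patients, 64 per group. The allowance follows: "Allowing a drop-out rate of 20% during the study, a total of 154 patients should be included".

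The figure of 161 is the trial's headline size. The abstract has "161 adult patients scheduled for elective gastrointestinal or lung cancer surgery", and Table 1 (trial registration data set) lists 161 as the target sample size.

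**The concern.** A drop-out rate is a share of the patients who are included. If a fraction d is lost, n patients remain only when n / (1 − d) are included. Multiplying by (1 + d) always gives too few, because the loss is then taken from a larger number than the one to which the allowance was added. Both totals in the section look like the result of multiplying by 1.20.

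At the drop-out rate the plan itself assumes, the trial would then end below its own stated minimum, and the 80% power would not be the power that goes with 161 patients. A reader of the abstract or registration table would take 161 as sufficient for 80% power at 20% loss.

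**Working it through.** **Inputs (all from the Sample size section, except allocation, which is in Randomization and blinding).** Two-sided alpha 0.05 (z = 1.960); power 0.80 (z = 0.842); standardized effect 0.40; within-subject correlation 0.6; 5 follow-up measurements; 1:1 allocation; drop-out 20%. For physical activity: effect 0.50, 128 required.

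**Step 1: reproduce the base number.** The body of Formula 1 is not visible in the text available, so its form is inferred from the inputs. The usual formula for the mean of m equally correlated follow-up scores is

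n per group = 2(z₁ + z₂)² / ES² × [1 + (m − 1)ρ] / m

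- 2 × (1.960 + 0.842)² / 0.40² = 98.11
- [1 + 4 × 0.6] / 5 = 0.68
- 98.11 × 0.68 = 66.7, rounded up to 67 per group, 134 in total

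This matches the plan.

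**Step 2: the drop-out step.**

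| | Required after drop-out | × 1.20 | ÷ 0.80 | Printed |
|---|---|---|---|---|
| Physical functioning | 134 | 160.8 → 161 | 167.5 → 168 | 161 |
| Physical activity | 128 | 153.6 → 154 | 160 | 154 |

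Both printed totals match multiplication and neither matches division. Two matches in the same section rule out rounding as the explanation.

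**Step 3: what the printed totals leave.**

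- 161 × 0.80 = 128.8 (64.4 per group), 5.2 below 134
- 1 − 134/161 = 16.8%, the largest drop-out at which 161 still leaves 134
- 154 × 0.80 = 123.2 (about 62 per group), 4.8 below 128
- 168 − 161 = 7 patients, or 7/161 = 4.3%

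**Step 4: power on the same formula.** Power = Φ(√(n × ES² / (2 × 0.68)) − 1.960), with n per group.

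- n = 67: √(67 × 0.16 / 1.36) = 2.808; power 80.2%
- n = 64.4: √(64.4 × 0.16 / 1.36) = 2.753; power 78.6%
- n = 64: √(64 × 0.16 / 1.36) = 2.744; power 78.3%

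For physical activity, a two-sample t-test with effect 0.50 gives 80.1% at 64 per group, as the plan intends, and 78.9% at 62 per group. The trial's target of 161 leaves 128.8 for this outcome, just above the 128 required.

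**The case against.** The strongest reply is that the shortfall probably does not exist in the analysis that will be run. The 78% treats each drop-out as contributing nothing and ignores baseline. The Statistical analysis section plans a linear mixed model over all postoperative measurements, by intention to treat, adjusted for the baseline score.

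- *Partial follow-up.* Assume a constant effect, correlation 0.6 and uninformative drop-out. A patient with one follow-up score then carries 0.68 / 1.00 = 68% of a completer's information. The gap of 5.2 completers closes if 5.2 / 0.68 = 7.6, about 8, of the 32 drop-outs return one questionnaire. If 16 do, the effective number is 128.8 + 16 × 0.68 = 139.7 and power is about 82%.
- *Baseline adjustment.* The documents give no baseline-to-follow-up correlation, so only a range can be shown. Replacing 0.68 by 0.68 − r² at 64 per group gives 78.9% for r = 0.1, 80.7% for 0.2, 83.8% for 0.3, 88.1% for 0.4 and 97.9% for 0.6. A correlation of about 0.2 restores 80%.

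Further, the effect size and correlation are themselves assumptions, and modest changes in them move power by more than 1.5 points. The 154 has no consequence for the trial, since the target is 161.

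All of this stands as a statement about size, and it shows that the trial is not materially underpowered by this slip. It does not reconcile the printed figures. The plan fixed 134 as the minimum, added an allowance meant to protect it, and took credit for neither partial data nor baseline. Nothing in the article defines the 20% as a share of completers, which is the one reading under which 161 would be right. If the sponsor wishes to rely on the mixed model's gains, that is a different calculation and should be written down as one.

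**Conclusion.** The concern holds. By the plan's own inputs, 161 patients with 20% drop-out leave 128.8, not 134. Power is 78.3% to 78.6% against the stated 80%, and the stated power is kept only up to 16.8% drop-out. The size consistent with 20% drop-out and 80% power is 168 for physical functioning, and 160 for physical activity in place of 154.

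The power figures rest on the inferred form of Formula 1, which reproduces 67 per group, and on counting drop-outs as lost entirely, as the plan's allowance does. The count of 168 needs neither a power formula nor its inputs; it follows from 134 and 20% alone. The loss is small, 7 patients and about 1.5 points of power, and the planned analysis may well recover it. This is an error in a stated figure, not a threat to the design.

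**What to change.** Choose one of two corrections for the primary outcome.

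1. **Keep 161 and restate what it delivers:** with 161 randomized and 20% drop-out, power is about 78% by Formula 1; 80% power is kept up to 16.8% drop-out. The gain expected from baseline adjustment and partial follow-up may be stated alongside, with the correlation assumed, so that the reader sees the practical loss is small. This costs one sentence and no patients. The abstract and Table 1 stay as they are, since 161 remains the target.
2. **Keep 20% drop-out with 80% power and change the target to 168.** This costs 7 more patients and an update of the abstract, Table 1 and the registry entry. The Recruitment section's own target of about 10 per month over 18 months, roughly 180, would accommodate it.

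In either case, replace 154 by 160 in the physical activity calculation, and note that the overall target covers it. That change is editorial.

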### Intervention

The intervention is described according to the template for intervention description and replication (TIDIER) checklist (See Supplementary File 1). The main purpose of the OPRAH intervention is to facilitate faster and better recovery in physical functioning by stimulating patients’ self-management regarding their level of physical activity and protein intake after hospital discharge.

#### Development of the intervention

The Medical Research Council (MRC) framework for the development and evaluation of complex intervention was used [28]. Supplementary File 3 shows the stages of the MRC framework alongside with our activities of the development process and the activities that are described in this paper. The intervention development process was guided by findings from a feasibility study [29], systematic review of literature on the effectiveness of intervention components [22], a literature search about barriers and facilitators to the targeted behavior and expert meetings with researchers and health professionals (OPRAH consortium, consisting of physiotherapists, dieticians, surgeons, researchers and a specialist in behavioral change). The behavioral change wheel was used as theoretical underpinning of the intervention [30]; with the use of this theory, we have been able to substantiate how the intervention causes change, what the active ingredients of the intervention are and how they can exert their effect. A feasibility study was conducted to evaluate the practical effectiveness.

The basis of the intervention was an existing app with a self-monitoring function of physical activity, which had been investigated in the postoperative period of oncological patients through a feasibility study [29]. Self-monitoring appeared to be feasible in this population. However, some patients emphasized the need for more support in addition to self-monitoring. This finding was strengthened by the results from our systematic review, because interventions with activity trackers in combination with coaching by a health professional seemed to be more effective in increasing physical activity during and after hospitalization [22]. In addition, the use of more behavioral change techniques (BCT’s) within the intervention was also suggested to be more effective.

Because of the important synergy between protein intake and physical activity after major oncological surgery, the app has been expanded with a self-monitoring tool for protein intake. By conducting a comprehensive literature search, barriers and facilitators to the targeted behaviors, improving physical activity and protein intake, were identified. Based on the behavioral change wheel and with input from the OPRAH consortium, a total of 15 behavioral change techniques, following the BCT taxonomy of Michie et al. [31], were identified and linked to a mode of delivery in order to target the desired behavior. (See Table 2) In Supplementary File 4, the BCTs are linked to the Capability, Opportunity, Motivation and Behavior (COM-B) model [30], intervention functions and mode of delivery. In order to improve the motivation of patients for behavioral change, motivational interviewing (MI) and shared decision making (SDM) was incorporated in the intervention. Based on initial feedback from the OPRAH consortium, the intervention was refined in preparation for evaluation.

**Table 2 Tab2:** Intervention components based on the BCT taxonomy (v1) of 93 hierarchically cluster techniques from Michie et al. [31]

Behavioral change technique	Description
**1.1 Goal setting (behavior)**	Patients are able to set goals on the amount of physical activity per day. Patients will be supported by the physiotherapist to set realistic goals Goals on requirements of protein intake will be set based on advice of the dietician
**1.2 Problem solving**	The physiotherapist/dietician analysis factors influencing the behavior and select strategies for overcoming barriers/increasing facilitator to perform behavior
**1.4 Action planning**	Patients are able to set in-app tasks. Patients will be encouraged by the physiotherapist/dietician to plan the performance (when, what time etc.)
**1.5 Review behavioral goals**	The physiotherapist/dietician will review the behavioral goals and consider modifying goals based on their achievement
**1.6 Discrepancy between current behavior and goal**	Visual in-app presentation of behavior and targeted goals
**2.2 Feedback on behavior**	The amount of minutes patients have to be active to achieve their goal is presented in the app. The number of points remaining to achieve protein requirements is shown In addition, the physiotherapist/dietician will give the patient feedback about their activity/intake
**2.3 Self-monitoring of behavior**	Patients are able to monitor their daily level of physical activity and protein intake via the app
**3.1 Social support**	Patients are able to request contact with the physiotherapist/dietician via the app The physiotherapist/dietician will contact the patient (how often is determined in consultation with the patient)
**4.1 Instructions on how to perform the behavior**	Tailored in-app information and personalized instructions by physiotherapist/dietician
**5.1 Instructions about health consequences**	Tailored in-app information and personalized instructions by physiotherapist/dietician
**7.1 Prompts/cues**	Patients can have the opportunity to receive in-app reminders to reach their daily goal
**8.7 Graded tasks**	The physiotherapists stimulate patients to set easy-to-perform tasks
**10.4 Social reward**	Physiotherapist/dietician reward the patients if there has been effort in performing the behavior
**10.5 Social incentive**	Patients receive in-app rewards if they achieved their goal
**12.5 Adding objects to the environment**	Wearing the PAM sensor

#### Coaching by health professionals

Coaching is an important part of the intervention, as the use of self-monitoring has proven to be more effective when combined with coaching by a healthcare professional and is considered important to improve the synergy and collaboration between physiotherapy and dietetics. Through the use of coaching, the intervention can be tailored to the clinical status of the patient. In addition, potential barriers to the desired behavior can be identified and, if they are within the scope of physiotherapist and dietician, addressed in collaboration with the patient. To support the physiotherapists and dieticians in coaching, the choice has been made to use motivational interviewing (MI) and shared decision making (SDM). MI increases patient autonomy, enhances intrinsic motivation and supports the patient’s self-efficacy all of which contributes to increasing the patient’s self-management [32]. A recent review indicated that MI is a powerful intervention in combination with self-monitoring using activity trackers to improve autonomous motivation and to reduce a-motivation for physical activity [33]. Furthermore, it was indicated that the delivery of the intervention can vary from telephone to real life coaching and can still be effective in impacting motivation, regardless of the delivery method [33]. SDM provides an opportunity to integrate evidence and patient preferences into a health-related decision [34, 35]. The physiotherapist and dieticians involved in this study have received a training about MI and SDM prior to the start of the study. The main purpose of this 3-day training course was to teach strategies according to the principles of MI to encourage patients to adopt healthy behavior, especially focused on physical activity and protein intake. In the first session, attention was paid to reflective listening; i.e. listening carefully to what the patient says and giving it back to the patient in different words in order to create understanding and clarity. Next, it was discussed what ambivalence is and how it can be recognized. Ambivalence means being pulled back and forth between the disadvantages and advantages of the current situation and the new situation. In the second session, the recognition of ambivalence was continued and conversation techniques were applied in order to guide the patient towards healthy behavior. During the last training day, all techniques were practiced with the help of a trained actor. Between the training days, the physiotherapists and dieticians applied the learned techniques in practice and reflected on this in duo sessions. To keep their knowledge and skills up to date during the study period, peer review meetings will be organized.

#### E-health technology

The Atris software (Peercode B.V. Geldermalsen, the Netherlands) is the investigational software used in the intervention. In combination with the ankle-worn PAM AM400 three-axis accelerometer (PAM B.V. Doorwerth, the Netherlands), the Atris software is used for self-monitoring of physical activity and protein intake. The Atris software consists of an Atris app for patients, Atris backend website for health professionals and the Atris (triggers) software. The Atris app allows patients to self-monitor their daily physical activity and protein intake through wearing the PAM and tracking daily protein intake by using a simple in-app self-registration system. See Fig. 3 for screenshots of the app and Supplementary File 2 for a subscript of the screenshots. Physical activity is represented in active minutes per day, with a distinction in low (1.4–2.99 metabolic equivalents of energy expenditure (METs)), moderate (3–7 METs), and vigorous activity (> 7 METs). The protein intake is represented in stars (★), where 1 star represents approximately 5 g of protein. The Atris app provides feedback on progress related to their goals. In addition, patients can ask questions through the app’s chat feature and receive response and information by the physiotherapist or dietician. Via the Atris backend website, the physiotherapist and dietician can interactively view patient data, send messages to the patient, and can access Atris (triggers) through the patient monitor. The software Atris (triggers) enables personalized goal setting and threshold values per patient.

**Fig. 3 Fig3:**
[figure not shown]
Screenshots of the Atris app

#### Intervention description and procedures

One week prior to planned surgery, patients receive the PAM and will receive access to and get instructions about the Atris app to get familiarized with the application. Patients are asked to wear the PAM 24 h a day in a strap around the ankle, from at least 5 days prior to surgery until 3 months after surgery. During hospitalization, the treating physiotherapist and dietician guide the patients in the use of the app during their standard consultations. As the day of hospital discharge approaches, the patient will be supported by the physiotherapists and dietician using the SDM process to set goals on active minutes and protein intake for after discharge. After discharge to home, patients are coached remotely (by telephone and chat) by a physiotherapist and dietician about physical activity and protein intake during 3 months after discharge. Through a chat function in the app, patients can ask questions to the physiotherapist or dietician, the physiotherapist and dietician can also send information through the chat. The ultimate goal for physical activity is to return to pre-surgery level of physical activity. The ultimate goal for protein intake is to achieve the personal daily requirements. If the recovery stagnates and goals are not achieved, the physiotherapist or dietician will contact the patient to identify barriers in their recovery. The sub-goals and the degree of coaching will be tailored using a SDM process to the personal needs and preferences of the patient. To support patients’ self-management, MI techniques will be applied during the coaching sessions with the physiotherapist and dietician by telephone and chat [32].

#### Criteria for discontinuing the intervention

Patients may discontinue the intervention in the following cases:Completion of the intervention period: Patients may discontinue the intervention once they have completed the predetermined duration of the OPRAH intervention (3 months after hospital discharge).Adverse effects or complications: If patients experience any adverse effects or complications directly related to the intervention, it may be necessary to discontinue their participation for safety reasons.Lack of adherence: If patients consistently fail to comply with the requirements or recommendations of the intervention, discontinuation will be considered. This can include non-engagement with wearing the PAM sensor or registration of their protein intake.Patient’s request or withdrawal: Patients have the right to choose whether they want to continue or discontinue the intervention. If a patient decides to withdraw from the program, their participation will be discontinued.

### Usual care

Both participants in the intervention and the control group receive usual care.

During hospitalization, patients are treated according to the Early Recovery After Surgery (ERAS) protocol [36]. This includes early mobilization and (nutritional) intake supported by the entire (para)medical team. In the daily consultations by the medical doctor and nursing staff, attention is paid to the improvement of mobilization and intake. The amount of consultation by the physiotherapist and dietician is determined based on the clinical assessment of the physiotherapist and dietician.

After hospital discharge, there is no usual physiotherapy care. The physiotherapist may advise the patient to continue physiotherapy in primary care, based on the clinical assessment of the physiotherapist. The usual care of the dietician differs between patient groups. In Amsterdam UMC, the dietician standard schedules postoperative consultations with patients after esophagus-, stomach-, pancreas-, biliair and Hypertherme Intraperitoneale Chemotherapy (HIPEC) cancer surgery at 2 and 4 weeks and 3 and 6 months after discharge. At St. Antonius, the dietician only schedules standard postoperative consultations at 2 weeks after discharge for patients after pancreas surgery. When necessary, more consultations can be planned. Patients after hepatic, colorectal (excl. HIPEC) or lung cancer surgery receive postoperative consultations by the dietician only on indication or the dietician may advise the patient to continue dietetic treatment in primary care. All participants are permitted to engage any form of (para)medical care during the study period.

